## Abstract

**Background:**

Dementia is a common and complex condition. Evidence-based guidelines for the management of people with dementia in general practice exist; however, detection, diagnosis and disclosure of dementia have been identified as potential evidence-practice gaps. Interventions to implement guidelines into practice have had varying success. The use of theory in designing implementation interventions has been limited, but is advocated because of its potential to yield more effective interventions and aid understanding of factors modifying the magnitude of intervention effects across trials. This protocol describes methods of a randomised trial that tests a theory-informed implementation intervention that, if effective, may provide benefits for patients with dementia and their carers.

**Aims:**

This trial aims to estimate the effectiveness of a theory-informed intervention to increase GPs’ (in Victoria, Australia) adherence to a clinical guideline for the detection, diagnosis, and management of dementia in general practice, compared with providing GPs with a printed copy of the guideline. Primary objectives include testing if the intervention is effective in increasing the percentage of patients with suspected cognitive impairment who receive care consistent with two key guideline recommendations: receipt of a i) formal cognitive assessment, and ii) depression assessment using a validated scale (primary outcomes for the trial).

**Methods:**

The design is a parallel cluster randomised trial, with clusters being general practices. We aim to recruit 60 practices per group. Practices will be randomised to the intervention and control groups using restricted randomisation. Patients meeting the inclusion criteria, and GPs’ detection and diagnosis behaviours directed toward these patients, will be identified and measured via an electronic search of the medical records nine months after the start of the intervention. Practitioners in the control group will receive a printed copy of the guideline. In addition to receipt of the printed guideline, practitioners in the intervention group will be invited to participate in an interactive, opinion leader-led, educational face-to-face workshop. The theory-informed intervention aims to address identified barriers to and enablers of implementation of recommendations. Researchers responsible for identifying the cohort of patients with suspected cognitive impairment, and their detection and diagnosis outcomes, will be blind to group allocation.

**Trial registration:**

Australian New Zealand Clinical Trials Registry: ACTRN12611001032943 (date registered 28 September, 2011).

## Background

Dementia is a global problem largely driven by population ageing. A recent review of the worldwide prevalence of dementia in those aged 60 years and over found that the age standardised rates varied from 4.19% to 8.5%. In 2010, the number of people with dementia was 35.56 million, and this number is expected to increase to 115.38 million by 2050 [1]. In 2011, there were an estimated 298,000 Australians with dementia, 74% of whom were aged 75 years and older. The number of Australians with dementia is projected to reach 900,000 by 2050 [2].

Evidence-based clinical practice guidelines (CPGs) for the management of people with dementia have been published by a number of agencies, including the Scottish Intercollegiate Guidelines Network (SIGN) [3]. These guidelines include a series of evidence-based recommendations for the detection, diagnosis and management of people with dementia, both in the community and in residential care, and focus on investigations and interventions which have been shown from research to directly benefit people with dementia. We undertook a systematic search (January 2012) for clinical practice guidelines published subsequent to the SIGN guideline and identified 14, the majority of which share the same recommendations. The IRIS (Implementing Research Implementation Strategies) trial focuses primarily on detection and diagnosis recommendations from the SIGN guideline, with some adaptation for the Australian context, and two recommendations considered best practice by the IRIS clinical investigators (Table 1).

**Table 1 T1:** Recommendations of the IRIS trial

**Recommendation**	**Details and source**
*Detection and diagnosis*	
Conduct a cognitive assessment using the Mini Mental State Examination (MMSE) in individuals with suspected cognitive impairment.	SIGN guideline (grade B recommendation*) [3].
Assess for co-morbid depression using a validated tool.	SIGN guideline (grade B recommendation*) [3]. We include the following as validated scales: Geriatric Depression Scale (GDS), Hamilton Rating Scale for Depression, and Even Briefer Assessment Scale for Depression.
Refer to Cognitive, Dementia and Memory Service (CDAMS) or specialist for access to dementia-modifying medications.	Local adaptation of SIGN guideline (grade B recommendation*) [3]. Guideline makes recommendations about specific pharmacological interventions (*e*.*g*., use of cholinesterase inhibitors). Access to dementia-modifying medication is via specialist referral in Australia.
Refer for head/brain computed tomography (CT) scan.	SIGN guideline (grade C recommendation*) [3]. Guideline recommends structural imaging. We focus only on referral for CT scan since GPs in Australia cannot refer for a MediCare rebatable magnetic resonance imaging.
Review current medication (prescription and over the counter) that may cause cognitive impairment.	Not a recommendation of the SIGN guideline. Considered best practice by the IRIS clinical investigators^†^.
Refer for pathology testing.	SIGN guideline (good practice point^‡^) [3]. Supported by other guidelines and considered best practice by the IRIS clinical investigators^†^.
*Management*	
Disclose or reinforce a diagnosis of dementia.	Not a recommendation of the SIGN guideline [3]. The SIGN guideline recommends that healthcare professionals should be aware that many people with dementia can understand their diagnosis, receive information and be involved in decision-making (grade C recommendation); that some people with dementia may not wish to know their diagnosis (grade C recommendation); and that in some situations, disclosure of a diagnosis of dementia may be inappropriate (grade D recommendation). Supported by other guidelines and considered best practice by the IRIS clinical investigators^†^.

*Grade of recommendation relates to the strength of evidence underlying the recommendation. Recommendations range from A to D, with A providing the highest level of evidence. Details of the types of evidence underlying each grade are available in the SIGN guideline [3] (pg. 2).

†Recommendation arrived at through discussion and consensus among the IRIS clinical investigators.

‡Recommended best practice based on the clinical experience of the SIGN guideline development group [3].

Detection, diagnosis and disclosure of dementia have been identified as potential evidence-practice gaps in Australian general medical practice [4,5]. Delayed diagnosis of dementia and delay in the recognition of dementia by GPs can impact outcome and restrict access to support for people with dementia and their carers. Early diagnosis can facilitate timely referral to education, counselling and support services for people with dementia and their carers, and early diagnosis is more likely to allow input from the patients about their care plans [6]. For example, there is evidence that caregiver interventions to improve well-being can delay entry to residential aged care in people with dementia [7]. Early differential diagnosis is also important in maximising the benefits of treatments and assists the patient and carer in understanding the prognosis of the disease [8]. Time from first suspicion of cognitive impairment by a GP to confirmed diagnosis or exclusion of dementia is considered too long and may take years [9]. International studies have estimated the average time from first symptoms to diagnosis, as reported by informants, to be between one and three years [10,11], with symptoms recorded in GPs’ medical records as early as five years before diagnosis [12]. A systematic review of qualitative studies suggests that diagnostic uncertainty or insufficient knowledge or experience, difficulties in disclosing the diagnosis, and the stigma attached to dementia, are barriers to diagnosis of dementia reported by primary care practitioners [13].

A limited number of randomised trials have tested the effectiveness of interventions to increase GPs’ awareness and diagnosis of people with suspected cognitive impairment and management of dementia [14-19]. These trials have evaluated a range of interventions (*e*.*g*., educational interventions, decision support software, practice-based workshops, blended learning), across different settings (United Kingdom, United States, Germany and France). The intervention effects from these trials have been mixed.

More generally, interventions designed to implement guidelines into practice have had varying success [20]. It has been suggested that this may be due, in part, to a lack of explicit rationale for the intervention choice, or the use of inappropriate methods to design the interventions [21-23]. Using theory to inform the design of interventions to implement guidelines into practice may provide a more effective approach [24]. In addition, theory provides a framework that can aid identification of factors that may modify the magnitude of intervention effects across trials [25,26]. The Theoretical Domains Framework of behaviour change provides a comprehensive framework for designing such interventions, offering broad coverage of potential change pathways [27].

A number of randomised trials are currently underway aiming to improve the management of dementia [28-31]. However, to our knowledge, no study in the Australian setting has investigated a theory-informed intervention to improve clinical practice in primary care in relation to detection and diagnosis of dementia.

### Aim and objectives

The aim of the IRIS trial is to determine if a theory-informed behaviour change intervention is effective in increasing GPs’ adherence to a clinical practice guideline for the detection, diagnosis and management of dementia in general practice (in Victoria, Australia). Our primary objectives are to establish if the intervention is effective in increasing the percentage of patients with suspected cognitive impairment who receive:

1. Cognitive assessment using the Mini Mental State Examination (MMSE); and,

2. Depression assessment using a validated scale.

These objectives reflect two key recommendations of the SIGN guideline for improving the detection and diagnosis of dementia (with level B evidence), for which there are identified evidence-practice gaps.

Secondary objectives include estimating the effects of the intervention for secondary outcomes in the categories of: GP diagnosis behaviours; proxy measures of GP diagnosis and management behaviours; and hypothesised mediators of GP behaviour (measures of motivation, capability, and opportunity to behave in a manner consistent with recommended behaviours [32]). In addition, we will conduct cost-effectiveness analyses to quantify the tradeoff between the hypothesised improvement in clinical practice and the additional costs (savings) arising from delivery of the intervention and from any subsequent changes in clinical practice and healthcare utilization within the trial period.

## Methods

The methods of the IRIS trial draw upon those of our previous implementation trials conducted in primary care settings [33,34]. At the time of submission of the trial protocol, the trial intervention has been delivered, and the baseline questionnaire measuring predictors of GPs’ diagnostic and management behaviours have been collected. Collection of patient level data has just begun (April 16).

### Trial design

The design of this trial is a parallel cluster randomised trial (C-RT) with clusters being general practices, including one or more GPs and their patients. A cluster randomised design was chosen since the intervention was targeted at GPs. Clustering at the level of the practice allows evaluation of the intervention as it would be delivered in a real world context, evaluating the direct effect of the intervention in combination with any ‘contamination’ effect arising from diffusion of the intervention amongst GPs within the same practice [35].

### Eligibility and recruitment

#### Recruitment of general practices

All GPs within the state of Victoria, Australia, listed on the Australasian Medical Publishing Company (AMPCo) database as of September 30, 2011, will be approached to participate in the trial. The AMPCo database is created from an amalgamation of sources and provides a comprehensive list of GPs in Australia. Practitioners will receive a letter of invitation, including an explanatory statement and consent form. Those who do not respond will be sent a maximum of four reminder letters, between September 2011 and February 2012. When a first GP in a practice agrees to participate, he or she will be sent invitation letters to distribute to GP colleagues who work in the same practice to facilitate more GPs to enrol per practice.

To increase awareness of the trial, notices will be placed in the newsletters of the Divisions of General Practice and Royal Australasian College of General Practitioners. Strategies to promote participation include offering continuing medical education points and an opportunity to enhance the detection and diagnosis of people with suspected cognitive impairment and their ongoing management. Practitioners will be provided with an honorarium (AUD 300) as a contribution toward practice staff time in running the electronic search of the medical records.

#### Identification of patients

Patients will be identified through an electronic search of the GPs’ medical records. We will receive de-identified data extracted from the medical records, and patients will not be contacted for any information. For these reasons, and because of the nature of the intervention (see ‘Interventions’ section), patients will not be consented to participate in the trial. This is consistent with Recommendation 3 of ‘The Ottawa Statement on the Ethical Design and Conduct of Cluster Randomized Trials’ [36], in that patients in this trial do not meet the criteria to be considered research participants.

A search module has been specifically developed as part of Pen Computer Systems (Pty Ltd) Clinical Audit Tool™ (CAT). The CAT was developed to analyse clinical information captured within general practice clinical desktop systems (*e*.*g*., Medical Director). Many Divisions of General Practice (renamed Medicare Locals in June 2012) within Victoria subscribe to the CAT, providing free access for practices within their jurisdiction. The developed module will only be activated in participating general practices, and when run, will yield a data file including all patients aged 70 years and older. The file will include demographic data (age and sex), coded diagnoses of cognitive impairment and dementia, extracted free text and dates related to cognitive and depression assessment and referral for CT scan and specialist services. To maintain anonymity of the patients, the extracted free text will be a maximum of 40 characters in length surrounding identified search terms. Search terms were compiled with input from the IRIS clinical investigators.

The search module will be run nine months after the start of the intervention (delivery of a workshop), and will search the medical records over the previous three years. From the extracted data, two cohorts of patients will be identified. The first cohort (cohort 1) will include all patients aged 70 years and older at baseline (June 22, 2012), but without a diagnosis of dementia. The second, and primary cohort of interest (cohort 2), will include the subset of cohort 1 patients for whom the GP has noted a suspicion of cognitive impairment in the medical records in the period prior to intervention delivery (prior to June 22, 2012). These patients will be identified through coded fields (*e*.*g*., coded diagnosis of cognitive impairment) and review of free text entries. Two researchers (with healthcare qualifications), who are blind to the intervention group, will independently review the free text entries. Disagreements will be resolved via discussion with a geriatrician who will not be informed of the group allocation of the patient.

The different cohorts will be used to examine GPs’ clinical behaviour with all older people (cohort 1) and with those patients whom the GP previously suspected of having cognitive impairment (cohort 2). Inclusion of the former cohort allows examination of whether the intervention is effective in raising GPs’ awareness and diagnosis of cognitive impairment and dementia in all older patients (including those with and without previously noted cognitive impairment).

#### Inclusion criteria

General practices will be included if the following criteria are met:

1. The practice is located in the state of Victoria, Australia.

2. At least one GP within the practice provides written informed consent.

3. The practice utilises a CAT-compatible general practice clinical desktop system (either Medical Director or Best Practice).

General practitioners will be included if the following criteria are met:

1. The GP works in a participating practice.

2. The GP provides written informed consent.

Patients will be included in cohort 1 if the following criteria are met:

1. The patient is ‘active’ (where ‘active’ is defined as a minimum of three visits recorded in the general practice clinical desktop system in the two-year period preceding follow-up [nine months after the start of the intervention]).

2. The patient is aged 70 years or older at baseline.

3. The patient visits the GP in the follow-up period (nine months after the start of the intervention).

Patients will be included in cohort 2 (those with suspected cognitive impairment) if any of the following additional criteria are met in the two-year period prior to the start of the intervention:

1. The patient has a coded diagnosis of cognitive impairment or free text indicating a suspicion of cognitive impairment (*e*.*g*., ‘confusion,’ ‘muddled’).

2. The patient has had an MMSE in isolation of a routine health assessment for people aged 75 years and older (75+ Health Check [37]) (an indication of the GP’s suspicion of cognitive impairment).

3. The patient has had an MMSE as part of a routine health assessment for people aged 75 years and older (75+ Health Check [37]) with a score that indicates cognitive impairment (*i*.*e*., a score between 10 and 24).

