#### Exclusion criteria

General practices will be excluded if the practice principal or practice manager refuses participation.

General practitioners will be excluded if they work at more than one of the general practices included in the trial.

Patients will be excluded from both cohorts 1 and 2 if, within the two-year period prior to the start of the intervention, the patient record has a coded diagnosis of dementia or contains free text indicating dementia (*e*.*g*., Alzheimer’s, senility, dementia). Patients with dementia will be excluded since only GPs’ detection and diagnosis (not management) behaviours of dementia can be measured through patient medical records.

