#### Timing of recruitment, intervention delivery, and follow-up

The intervention educational workshop took place on the June 23, 2012. The guidelines were sent to the control group GPs in November 2012. Questionnaires measuring predictors of GPs’ detection, diagnosis, and management behaviours were collected at baseline and will be collected nine months post the educational workshop (April 2013). The cohort of patients meeting the inclusion criteria for the trial, and GPs’ detection and diagnosis behaviours of these patients, will be identified and measured via the CAT nine months post the educational workshop (from April 2013). Figure 1 depicts the timing of recruitment, intervention delivery, and follow-up.

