### Outcome measurement

Table 4 provides a summary of the measurement tools. In brief, GPs’ detection and diagnostic behaviours will be measured through the CAT where possible. Proxy measures and mediators of GP behaviour will be measured through a paper-based questionnaire (available in Additional file 1 - IRIS behavioural construct questionnaire).

**Table 4 T4:** Summary of measurement tools

**Outcome or category of outcomes**	**Measurement tool**	**Details**
*GP behaviour*		
Cognitive assessment using MMSE	CAT electronic search^†^	MMSE results recorded in the patient file or free text indicates an MMSE has been undertaken.
Depression assessment using validated scale	CAT electronic search^†^	Geriatric Depression Scale (GDS) results recorded in the patient file or free text indicates GDS, Hamilton Rating Scale for Depression, Even Briefer Assessment Scale for Depression has been undertaken.
Referral to CDAMS or specialist	CAT electronic search^†^	Free text indicates that the patient has been referred to CDAMS, ACAS (Aged Care Assessment Service), or a geriatrician.
Referral for CT scan	CAT electronic search^†^	CT scan has been requested or free text indicates that a CT (head) scan has been requested/undertaken.
Dementia diagnosis	CAT electronic search^†^	Coded diagnosis of dementia or free text indicates that the patient has dementia or Alzheimer’s disease.
Cognitive assessment using MMSE (all patients aged 70+ years)	CAT electronic search^†^	MMSE results recorded in the patient file or free text indicates an MMSE has been undertaken.
Reported suspicion of cognitive impairment (all patients aged 70+ years)	CAT electronic search^†^	Coded diagnosis of cognitive impairment or free text indicates a suspicion of cognitive impairment (*e*.*g*., confusion, muddled, cognitive), or; MMSE undertaken in isolation of the 75+ Health Check (an indication of GP’s suspicion of cognitive impairment), or; MMSE undertaken as part of 75+ Health Check with score indicating cognitive impairment (*i*.*e*., a score between 10 and 24).
Dementia diagnosis (all patients aged 70+ years)	CAT electronic search^†^	Coded diagnosis of dementia or free text indicates that the patient has dementia or Alzheimer’s disease.
*Proxy measures of GP behaviour*		

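### Cohort 1 needs no visit before the workshop, so a patient who joins later with established dementia will normally count as a dementia diagnosis event

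*Protocol article*

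**What the plan says.** Under Inclusion criteria, cohort 1 has three entry rules:

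- the patient is active, meaning "a minimum of three visits recorded in the general practice clinical desktop system in the two-year period preceding follow-up";
- "The patient is aged 70 years or older at baseline";
- "The patient visits the GP in the follow-up period (nine months after the start of the intervention").

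The Exclusion criteria remove a patient from both cohorts if "within the two-year period prior to the start of the intervention, the patient record has a coded diagnosis of dementia or contains free text" pointing to dementia. The reason given there is that medical records can show detection and diagnosis behaviour but not management. Identification of patients describes cohort 1 as free of a dementia diagnosis. It says that including this cohort "allows examination of whether the intervention is effective in raising" GPs' awareness and diagnosis in all older patients, whether or not impairment was noted before.

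Table 2 lists dementia diagnosis in all patients aged 70 or older as a secondary outcome on cohort 1. Table 4 scores it from any qualifying entry: "Coded diagnosis of dementia or free text indicates that the patient has dementia or" Alzheimer's disease. It does not require that the entry be a first diagnosis. On timing, "The intervention educational workshop took place on the June 23, 2012", with the search of records nine months later, from April 2013.

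**The concern.** The entry rules and the exclusion look at different stretches of the record. Entry can be satisfied wholly after the workshop, while the exclusion looks only before it. For a patient with no earlier record at the practice, the exclusion has nothing to read. If that patient arrives with dementia diagnosed elsewhere and the new GP writes it down, Table 4 scores a dementia diagnosis.

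Such an event is the transcription of a history, not detection. It contradicts the description of cohort 1 as free of diagnosed dementia and the protocol's own reason for excluding dementia. At stake is the interpretation of one secondary outcome, the one meant to show whether the workshop leads GPs to diagnose more dementia among older patients generally. New diagnoses over nine months are likely to be few, so even a small number of carried-in cases could be a visible share of the events.

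**Working it through.** **Step 1. Compare the windows by date.** Take the workshop as 23 June 2012 and follow-up as 23 March 2013, nine months later.

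| Rule | Window | Part after the workshop |
|---|---|---|
| Active (three visits) | 23 March 2011 to 23 March 2013, 731 days | 273 days, 273/731 = 37% |
| Follow-up visit | 23 June 2012 to 23 March 2013 | all |
| Age 70 or older | at baseline, computable for anyone | not applicable |
| Dementia exclusion | two years up to the workshop | none |
| Dementia diagnosis outcome | nine months after the workshop | all |

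Three visits within the last 273 days satisfy the active rule and the follow-up visit rule together. Nothing in the list requires a record before 23 June 2012.

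**Step 2. Does cohort 2 share the gap?** No. Its additional criteria must be met in the two years before the intervention, so a later joiner does not normally qualify. The sample size rests on cohort 2 and reproduces: the design effect is 1 + ((0.7² + 1) × 20 − 1) × 0.10 = 3.88; 227 patients per group for 50% against 65% at 90% power gives 227 × 3.88 / 20 = 44.04, so 45 practices; 45 / 0.75 = 60. None of these inputs is affected.

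**Step 3. Illustrate the size.** The article gives no joiner rate and no rate of new diagnosis, so there is no figure of the plan's own to reproduce. Inputs:

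- *j*, share of cohort 1 that joins after the workshop: 1% to 8% (assumption);
- *p*, share of joiners with dementia: 4.19% to 8.5% (Background section, a worldwide figure for ages 60 and over, borrowed for illustration);
- *t*, true nine-month diagnosis rate in the control arm: 1% to 2% (assumption);
- true odds ratio 1.5 (assumption); *j* and *p* equal in both arms; every carried-in case is recorded in follow-up and none is caught by the exclusion.

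Carried-in events as a share of the cohort are *j* × *p*. The observed control risk is (1 − *j*) × *t* + *j* × *p*, which treats joiners as contributing only carried-in events. The share of control-arm events is *j* × *p* divided by that risk. The intervention arm uses the same formula with the risk implied by an odds ratio of 1.5, which is 1.493% when *t* = 1% and 2.970% when *t* = 2%.

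| *j* | *p* | *t* | Carried in per 1,000 | Share of control events | Observed odds ratio |
|---|---|---|---|---|---|
| 1% | 4.19% | 2% | 0.42 | 0.000419/0.02022 = 2.1% | 1.49 |
| 5% | 4.19% | 2% | 2.10 | 0.002095/0.02110 = 9.9% | 1.45 |
| 5% | 8.5% | 1% | 4.25 | 0.00425/0.01375 = 30.9% | 1.35 |
| 8% | 8.5% | 1% | 6.80 | 0.0068/0.0160 = 42.5% | 1.29 |

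If joiners without dementia are instead given the same new-diagnosis rate as everyone else, the last row becomes 0.0068/0.01673 = 40.6%, with an observed odds ratio of 1.30. The choice of formula matters little.

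**The case against.** Several points against this are fair, and they limit it.

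- **Impairment.** A reader might infer that joiners with known cognitive impairment are also wrongly kept in and scored as newly suspected. The article does not support that. Cohort 1 deliberately includes patients with previously noted impairment, and the outcome is reported suspicion, not new suspicion. An established patient whose impairment is noted again counts in the same way. No stated rule fails there.
- **Not absolute.** It would be too strong to say that such patients can never be excluded. A diagnosis entered with its original date, or an imported record, could fall inside the exclusion window. Blinded coders also read the free text. The article does not say how carried-over dates are treated, but blinding the coders does not create an earlier record where none exists.
- **Size.** The joiner share and diagnosis rate are assumptions. The prevalence covers all dementia, whereas only diagnosed dementia can be carried in, and the Background stresses late diagnosis. That pushes the illustration too high. The age range of 60 and over pushes it the other way for a cohort aged 70 or older. At the low end the effect is negligible.
- **Direction.** A reader might also infer a spurious benefit of the workshop. The rule is the same in both arms, so the expected effect is dilution. A false effect would need trained GPs to record incoming histories more fully. GPs are unblinded and the workshop targets their diagnostic behaviour, so this is possible, but nothing in the article shows it.
- **Breadth of remedy.** An MMSE done by a participating GP on a new patient is genuine behaviour of interest, so removing joiners from every cohort 1 outcome would go too far. This stands, and the fix below is limited accordingly.

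**Conclusion.** The gap is real but narrow. Applied as written, the cohort 1 rules admit late joiners with established dementia and normally score them as dementia diagnosis events, against the protocol's own description of the cohort. The consequence is misclassification in one secondary outcome, expected to dilute its odds ratio if joining and recording are equal in both arms.

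The size is unknown. Over the assumed ranges, a true odds ratio of 1.5 would read as 1.49 at the mild end and 1.29 at the extreme. The extreme needs the highest joiner share, the highest prevalence and the lowest diagnosis rate together, with all prevalent dementia already diagnosed and recorded. It marks an upper end and is not an estimate.

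**What to change.** For the cohort 1 dementia diagnosis outcome, add one condition: at least one visit to the practice recorded in the two years before the start of the intervention. Keep late joiners in the other cohort 1 outcomes (MMSE assessment and reported suspicion), and apply the same restriction there as a sensitivity analysis. Cohort 2 needs no change.

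The cost is one line in the definition and a small loss of late joiners from that outcome. The active rule and the follow-up visit rule already need visits counted within date windows, the search reaches back three years, and patient data collection had only just begun when the article was submitted. One point needs confirming: the article's list of extracted fields does not name visit dates, so the team should check that the search can supply this count. The condition will not remove every carried-in case, because one earlier visit does not guarantee that the history was recorded, but it gives the exclusion a record to read.
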